## Abstract

**Background:**

Perennial malaria chemoprevention (PMC) is a chemoprevention strategy endorsed by the World Health Organization (WHO) and is increasingly being adopted by National Malaria Programmes. PMC aims to reduce morbidity and mortality caused by malaria and anaemia in in young children through provision of antimalarial drugs at routine contact points with the local health system. This study aims to evaluate the impact of the programmatically-implemented country-tailored PMC programmes targeting children up to two years of age using sulfadoxine-pyrimethamine (SP) on the incidence of malaria and anaemia in children in Cameroon and Côte d’Ivoire.

**Methods:**

We will assess the impact of PMC using passive and active monitoring of a prospective observational cohort of children up to 36 months of age at recruitment in selected study sites in Cameroon and Côte d’Ivoire. The primary and secondary outcomes include malaria, anaemia and malnutrition incidence. We will also conduct a time-series analysis of passively detected malaria and anaemia cases comparing the periods before and after PMC introduction. This study is powered to detect a 30% and 40% reduction of malaria incidence compared to the standard of care in Cameroon and Côte d’Ivoire, respectively.

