## Background

Despite impressive reductions over the past 15 years, the burden of malaria-attributable morbidity and mortality has increased recently from an estimated 219 million malaria cases in 2019 to 249 million cases in 2022 [1–3]. Malaria deaths have followed the same trend with an increase from an estimated 568,000 in 2019 to 619,000 in 2021. Nearly all (96%) of these deaths occurred in 29 African countries. Although children under five years of age are most at risk of dying from malaria, children under two are estimated to account for one-third (36%) of global malaria deaths [2, 4].

In 2010, the World Health Organization (WHO) recommended the provision of three-doses of sulfadoxine-pyrimethamine (SP) in the first year of life, an intervention known as intermittent preventative treatment for malaria in infants (IPTi). A Cochrane review of placebo-controlled randomized controlled trials of IPTi showed the intervention reduced clinical malaria by 30% (rate ratio [RR] 0.70, 95% confidence interval (CI) 0.62 to 0.88), anaemia by 18% (RR 0.82, 95% CI 0.68 to 0.98), and parasitaemia by 34% (RR of 0.66, 95% CI: 0.56–0.79) [5]. However, parasite resistance to SP has undermined confidence in the use of this drug for national policy: This might explain why only one malaria-endemic country, Sierra Leone, has adopted IPTi over the past decade [6]. Since the initial WHO recommendation, new data suggest that expanding the number of doses of SP, as well as increasing the age of eligible children beyond the first year of life may confer enhanced protection [2, 7, 8]. Prompted by these findings in 2022, the WHO recommended the provision of perennial malaria chemoprevention (PMC) [9, 10]. The PMC intervention involves the administration of a full treatment-course of an antimalarial drug at predefined age intervals, regardless of infection, as a chemoprevention strategy in areas with high perennial transmission. Per WHO guidelines, the PMC schedule should be informed by the age pattern of severe malaria cases, the duration of protection of the selected antimalarial, and the feasibility and affordability of delivering each additional PMC course [9]. However, to understand whether investing in PMC represents an effective use of scarce resources, rigorous evidence on its potential effectiveness at reducing malaria and anaemia incidence is needed.

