### Passive cohort

All children up to 36 months of age residing in enumerated households during the census will be eligible for inclusion in the passive cohort and enrolled upon provision of written informed consent from their primary caregiver (Table 1). Enrolled children will be passively monitored to record both EPI vaccinations and PMC visits as well as clinical visits for malaria and anaemia to the health facility and/or CHWs over the 18-month study period. Older children (24 to 36 months at baseline) are not eligible to receive the intervention but will be enrolled in this study activity for two reasons: first, the older children will serve as an internal control as it is assumed that they will experience a similar malaria transmission intensity but will not receive the intervention and, secondly, as children will be followed for 18 months information will be available on children who age-out of eligibility to assess any impact beyond when children are eligible to receive PMC. Children will not be censored according to age.

During the passive cohort recruitment, trained fieldworkers will record basic demographic information about the child, recent malaria cases, amongst other information. An anonymous and unique QR code with the participant ID linked will be attached to each child’s health and vaccination record books. This QR code will be used to identify children participating in the study when they interact with the health system and facilitate linking the data generated by the routine system on EPI, PMC or clinical visit, which are stored in separate registers, with the research activities. During recruitment, the national health ID number assigned to each child and written in the health and/or vaccination record books will be recorded. The names of children and primary caregivers will also be recorded to provide a means to verify that children present match ID numbers. This also serves as a back-up method to link health information data that is routinely collected in different registers. Caregivers will be encouraged to take children to the participating facilities or CHWs to receive EPI vaccinations or PMC or for any illnesses.

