Study staff will be present during the scheduled EPI visits to record when children received each dose of PMC. This may occur at health facilities or during active campaigns initiated by the health facility staff where vaccinations, including the newly introduced RTS, S vaccine where present, Vitamin A or SP is distributed. Data collected will include the child’s ID number, the date, location, and which health interventions were administered at that contact point. Where CHWs administer some of the SP or Vitamin A doses, they will record the data for the relevant contact point. The study staff will also collect, information on all clinical malaria and anaemia episodes throughout the 18-month study period. When a child participating in the passive cohort (i.e., has a QR code in their record book or the caregiver makes their participation known and confirmed through looking up their name) visits a study health facility or CHW, information about their visit will be recorded including date, diagnosis and treatment received and whether a referral was made. For children receiving inpatient treatment for anaemia or malaria, additional information including clinical symptoms and details of any complications, treatments received, the outcome, and date of discharge will be collected. Data will also be collected on any children who die in hospital during the study period. All data will be obtained from the clinical registries and confirmed by the facility staff.

Finally, to ensure that results are interpreted within the context of the broader trends in malaria transmission and the incidence of anaemia, routine surveillance data for each health facility will be collected up to five years before the start of the evaluation untill the end of the study. Data will consist of monthly aggregated data per health facility per 12-monthly age-band for children under 5 years of age. Key variables to be collected include the number of attendees, number of uncomplicated and complicated malaria cases, the number of malaria deaths, the number of anaemia and severe anaemia cases.

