### Active cohort

The active cohort will measure malaria infection, anaemia, and malnutrition incidence in the intervention and control study populations in Cameroon and Côte d’Ivoire. The sampling frame for the active cohort will consist of the children whose primary caregiver provided consent for participation in the passive cohort (Table 1). Children between 6 and 9 months and 10 weeks and 6 months of age at recruitment in Cameroon and Côte d’Ivoire, respectively, will be approached for inclusion. Targeting these age ranges will maximize study power to measure differences between the PMC intervention and standard of care in each country within the 18-month study period. The target age range was also defined to ensure at least one sampling time point after the final potential PMC dose to observe any change in risk of malaria infection after aging out of the intervention [13]. Recruitment into the active cohort will continue until the target sample size is achieved.

At the initial household visit for children enrolled in the active cohort, field workers will record the household and child ID number assigned during the census and collect detailed information related to malaria risk factors including household construction and use of vector control interventions. A detailed questionnaire on recent fevers, malaria history, care seeking behaviours, EPI vaccines received to date, and other relevant factors will also be collected. Children will be assessed for fever, anaemia, malaria, and malnutrition. First, forehead temperature will be taken using an infrared thermometer with fever defined as those with temperature > 37.5 °C. A capillary blood sample by heel or fingerpick will be collected using a sterile lancet and aseptic technique on all children. The blood sample will be used to measure: (i) haemoglobin (Hb) levels with a photometer (HemoCue^®^ Hb 301, Angleholm, Sweden), devices, (ii) conduct a malaria rapid diagnostic test (RDT), (iii) prepare a thin and thick blood slide for malaria microscopy and (iv) to collect blood spots on filter paper. The mid-upper-arm circumference will be collected from all enrolled children to screen for malnutrition and monitor growth trajectories over time. Treatment for malaria, anaemia and malnutrition will be offered according to national guidelines. Any children with a fever or who are severely ill will be referred to the nearest health facility for treatment.

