### Data analysis

The primary analysis will be based on intention to treat (ITT), including all children residing in the intervention area as the exposed group. All available data up to the time of censuring (e.g., loss to follow-up, withdrawal, death, or study completion), irrespective of whether the child received any, part, or all the intended PMC doses. An additional per-protocol analysis will be completed which includes children who received at least one dose, all doses, or specific doses of PMC. The period of protection provided by SP is up to one-month post treatment and thus will constitute the protective window of those receiving the intervention. Data for both countries will be combined for analysis as well as assessed separately to ensure context specific nuances are fully assessed.

Incidence rates for malaria and anaemia will be calculated using multivariable Poisson regression, difference-in-difference, and interrupted time-series models comparing intervention and control areas [14–16]. Incidence rates, rate differences, and rate ratios between intervention and control area will be calculated for the ITT and per-protocol analysis. Malaria incidence will be determined by the number of malaria cases confirmed by either RDT or microscopy identified in either the passive or active cohort. Person-time at risk for each study outcome will be calculated based on the date of recruitment into the study population until the date of censuring or study end. For children who leave the study prior to the end date, the date of exit will be the date where they moved, withdrew from the study, or died. If that date is not known, the midpoint between the date of last contact and the date the loss was detected will be used. Protective effectiveness will be calculated for the intervention period including the 18 months of follow-up for the periods where PMC doses differ, stratified by first and second year of life, as well as during the post-intervention period, starting at 24 or 18 months of age in Cameroon and Côte d’Ivoire, respectively, to estimate any potential rebound in malaria.

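### The planned anaemia time series counts diagnoses made at clinical visits, and if PMC reduces malaria visits, recorded anaemia can fall beyond any change in haemoglobin

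*Protocol article*

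**What the plan says.** The Abstract (Methods) announces the analysis: "We will also conduct a time-series analysis of passively detected malaria and anaemia cases comparing the periods before and after PMC introduction".

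The Passive cohort section shows where such cases come from. Children are monitored through vaccination and PMC contacts "as well as clinical visits for malaria and anaemia to the health facility and/or CHWs over the 18-month study period". On the source of the clinical information it says: "All data will be obtained from the clinical registries and confirmed by the facility staff". The pre-PMC history is facility surveillance going back up to five years: "Data will consist of monthly aggregated data per health facility per 12-monthly age-band for children under 5 years of age". Its variables include attendees, malaria cases and "the number of anaemia and severe anaemia cases". No haemoglobin test independent of illness is described in either passive stream.

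The Data analysis section then treats the two outcomes together: "Incidence rates for malaria and anaemia will be calculated using multivariable Poisson regression, difference-in-difference, and interrupted time-series models", comparing intervention and control areas. For malaria it goes on to state how a case is confirmed and that cases may come from either cohort. It has no matching sentence for anaemia.

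The active cohort is different. A blood sample is taken from every enrolled child, among other things to measure "haemoglobin (Hb) levels with a photometer". The procedure is repeated at three-monthly visits, up to seven in all.

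**The concern.** In the passive data, anaemia is counted only when a child attends and someone records the diagnosis. A malaria attendance is a natural occasion for that. An intervention designed to prevent malaria therefore acts on the outcome by two routes: it may truly reduce anaemia, and it reduces the number of times anaemia already present is noticed.

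The second route would appear where and when an effect is expected: in the intervention area, after PMC starts, at PMC ages. The usual protections of a time series with a comparison group do not help. The control area, the pre-PMC years and the older children used as an internal control adjust for trends that PMC does not cause. This change in detection is caused by PMC.

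The Aims and objectives section does say that passive detection is limited to care-seekers. It presents this as underestimating the malaria burden, not as detection of anaemia that shifts with the intervention. Anaemia appears in the stated aim in the abstract and among the secondary objectives, and the results are meant to inform programme decisions. A fall in the register series could be reported as an effect on anaemia when part of it is fewer occasions to find it.

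**Working it through.** The article gives no target effect, power or event count for the anaemia time series, so there is no planned figure to reproduce. The check is how large the artefact could be.

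**Inputs**
- r, the relative reduction in malaria visits. Set to the reductions in malaria incidence in the Sample size section: 0.30 in Cameroon, 0.40 in Côte d'Ivoire. That they carry over to clinic visits is an assumption.
- s, the share of recorded anaemia that is incidental (not caused by the malaria episode) and found at a malaria visit. Not in the documents; taken as 0.10 to 0.50.
- e, a relative rise in anaemia detections outside malaria visits. Not in the documents; taken as 0 or 0.10.

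**No offset, haemoglobin unchanged.** Ratio of recorded anaemia = 1 - s x r.

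| s | Cameroon (r = 0.30) | Côte d'Ivoire (r = 0.40) |
|---|---|---|
| 0.10 | 1 - 0.03 = 0.97 | 1 - 0.04 = 0.96 |
| 0.25 | 1 - 0.075 = 0.925 | 1 - 0.10 = 0.90 |
| 0.50 | 1 - 0.15 = 0.85 | 1 - 0.20 = 0.80 |

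The spurious fall is 3-15% in Cameroon and 4-20% in Côte d'Ivoire.

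**With an offset.** Ratio = (1 - s)(1 + e) + s(1 - r), with e = 0.10.

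| s | Cameroon | Côte d'Ivoire |
|---|---|---|
| 0.10 | 0.99 + 0.07 = 1.06 | 0.99 + 0.06 = 1.05 |
| 0.25 | 0.825 + 0.175 = 1.00 | 0.825 + 0.15 = 0.975 |
| 0.50 | 0.55 + 0.35 = 0.90 | 0.55 + 0.30 = 0.85 |

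A modest rise in other detections can cancel or reverse the artefact when s is small, but not when s is 0.50.

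**Scale.** The Background cites a review of infant trials in which preventive treatment reduced anaemia by 18%. An artefact of that size needs s = 0.18/0.30 = 0.60 in Cameroon or 0.18/0.40 = 0.45 in Côte d'Ivoire. The 18% is a yardstick only; it is not a target of this study.

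**The case against.** The strongest reply is that the design already contains the answer. The article says that active surveillance reduces the influence of care-seeking on measures of effect, uses both approaches for that reason, and measures haemoglobin in every active-cohort child. The routine series is collected partly as context. Ranking data sources for a secondary outcome is often left to an analysis plan, which is not shown here. Diagnosed anaemia is also a legitimate outcome in its own right, since fewer diagnoses mean less work for services.

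Most of this stands, and it limits the point to the passive analyses. It does not dispose of it: the abstract gives passively detected anaemia its own before/after analysis, and the Data analysis section gives anaemia the same models as malaria without saying which source carries the conclusion.

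A reader might infer more than the article supports:
- That the difference-in-difference model is known to rest on sick-visit anaemia. The Data analysis section assigns it no anaemia source. The only multi-year pre-PMC series is the facility counts, which makes this likely, but it remains an inference.
- That the bias is certain and away from the null. PMC delivery brings community and campaign contacts that could raise detection, and persistent anaemia missed at one visit may be found at a later one.
- That the artefact is as large as the effect sought. This needs s in the upper part of its possible range, r is borrowed from the planned effect on malaria incidence, and no anaemia target is stated.
- That a fall seen only at malaria visits is not an effect on anaemia. A true reduction in malarial anaemia would produce that very pattern, and malaria status at the visit is itself changed by PMC.

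**Conclusion.** The concern holds for the passive anaemia time series, and for the difference-in-difference model to the extent that it uses the same data. If PMC reduces malaria visits, recorded anaemia can fall in the intervention area beyond any change in haemoglobin, and no comparison in the design removes that part. Any such artefact would add to whatever true effect PMC has by preventing malarial anaemia.

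The size cannot be fixed from the article. Falls of 3-15% (Cameroon) and 4-20% (Côte d'Ivoire) rest on an assumed s of 0.10 to 0.50, on the planned malaria reductions applying to visits, and on no offset from other contacts or later detection. The active-cohort haemoglobin data, taken on a schedule that does not depend on illness, do not share the problem, so the anaemia evidence as a whole is not compromised. The primary malaria outcome lies outside this point.

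**What to change.** In the Data analysis section:
- State that the conclusion on anaemia incidence rests on haemoglobin measured in all active-cohort children at scheduled visits.
- Label the passive-cohort and routine series as clinically diagnosed anaemia. Treat them as supportive for that conclusion, and keep them as a service-burden outcome and for severe anaemia.
- Name the anaemia source for each of the three model types.
- Add a descriptive sensitivity analysis. Tabulate individual passive anaemia diagnoses by whether malaria was confirmed at the same visit, and show the routine series beside the attendee counts already collected. Note that PMC affects both malaria status and attendance, so neither display separates artefact from true effect. Attach no decision rule to the tabulation.

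The cost is wording and one tabulation from data already planned. The downside is that the passive anaemia time series carries less inferential weight.

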**Discussion:**

This multi-country study aims to provide evidence of the effectiveness of PMC targeting children in the first two years of life on malaria and anaemia and will provide important information to inform optimal operationalization and evaluation of this strategy.

**Trial Registration:**

Cameroon - NCT05889052; Côte d’Ivoire - NCT05856357.

**Supplementary Information:**

The online version contains supplementary material available at 10.1186/s12889-024-19887-8.

## Background

Despite impressive reductions over the past 15 years, the burden of malaria-attributable morbidity and mortality has increased recently from an estimated 219 million malaria cases in 2019 to 249 million cases in 2022 [1–3]. Malaria deaths have followed the same trend with an increase from an estimated 568,000 in 2019 to 619,000 in 2021. Nearly all (96%) of these deaths occurred in 29 African countries. Although children under five years of age are most at risk of dying from malaria, children under two are estimated to account for one-third (36%) of global malaria deaths [2, 4].

In 2010, the World Health Organization (WHO) recommended the provision of three-doses of sulfadoxine-pyrimethamine (SP) in the first year of life, an intervention known as intermittent preventative treatment for malaria in infants (IPTi). A Cochrane review of placebo-controlled randomized controlled trials of IPTi showed the intervention reduced clinical malaria by 30% (rate ratio [RR] 0.70, 95% confidence interval (CI) 0.62 to 0.88), anaemia by 18% (RR 0.82, 95% CI 0.68 to 0.98), and parasitaemia by 34% (RR of 0.66, 95% CI: 0.56–0.79) [5]. However, parasite resistance to SP has undermined confidence in the use of this drug for national policy: This might explain why only one malaria-endemic country, Sierra Leone, has adopted IPTi over the past decade [6]. Since the initial WHO recommendation, new data suggest that expanding the number of doses of SP, as well as increasing the age of eligible children beyond the first year of life may confer enhanced protection [2, 7, 8]. Prompted by these findings in 2022, the WHO recommended the provision of perennial malaria chemoprevention (PMC) [9, 10]. The PMC intervention involves the administration of a full treatment-course of an antimalarial drug at predefined age intervals, regardless of infection, as a chemoprevention strategy in areas with high perennial transmission. Per WHO guidelines, the PMC schedule should be informed by the age pattern of severe malaria cases, the duration of protection of the selected antimalarial, and the feasibility and affordability of delivering each additional PMC course [9]. However, to understand whether investing in PMC represents an effective use of scarce resources, rigorous evidence on its potential effectiveness at reducing malaria and anaemia incidence is needed.

